### Statistical considerations

Besides descriptive methods, complex statistical models will be used for statistical analysis of main and further outcomes because of the clustered data structure. For example, mixed effects regression models [52] or GEE models [54] will be used. Both procedures can be extended in an easy way to adjust for possible covariates, e.g. variables regarding the familial and social background of children or time span between time of baseline measurement and time of follow-up measurement.

Health-economic aspects will be evaluated in a similar way as performed for the project URMEL-ICE [37].

## Discussion

"Komm mit in das gesunde Boot - Grundschule" is the largest health promotion program for primary school children in Germany. One advantage is that the program pursues the aims and contents of the existing curriculum and supports school teacher with easy useable material and information. The intervention consists of units incorporated during lessons and recess. The program expands the former URMEL-ICE study approach [15,16,37] from the 2^nd ^grade to all grades of the primary school and to the whole state of Baden-Württemberg. This makes the dissemination process crucial. The research team decided to use a system of project delivery consultants which are educated at the program center and disseminate information and material and provide courses in their region. The dissemination process is very successful: the program is implemented in 427 primary schools across Baden-Württemberg and 890 primary school teachers took part in local training courses performed by the project delivery consultants in the academic years 2009/2010 and 2010/2011.

The program is easily feasible by the class teacher and the additional effort required is very low. No external experts and no additional physical education lessons are necessary. An important point is the investigation of efficacy of the intervention which is part of the program: for a lot of other prevention programs efficacy could not be shown [27,28]. For an evaluation of the efficacy of the intervention the Baden-Württemberg Study is performed. It is a prospective, stratified, cluster-randomized, longitudinal study with two groups. Stratified randomization was performed for primary schools in Baden-Württemberg, South West Germany, according to school type (number of classes and grade). Despite withdrawal of written consent from 7 teachers of 5 schools, there is an approximately balanced number of classes in intervention and control group at baseline: within 1^st ^grade classes (39:36), within 2^nd ^grade classes (32:29), and within mixed-grade classes (10:11). Because only three teachers refused written consent after baseline measurements, the approximate balance between schools remained stable at follow-up. At baseline the percentage of boys in both study groups is comparable within 1^st ^grade classes (50.1% and 50.6%) and within mixed-grade classes (58.5% and 58.9%). A difference in this percentage is observed within 2^nd ^grade classes (45.6% and 50.3%). Therefore, an adjustment for sex will be realized in the statistical analysis.

The Baden-Württemberg Study has numerous important methodological strengths: a cluster-randomized controlled design (waiting control group design) was implemented with an intervention group and a control group. Stratified randomization was performed and a balanced ratio of classes in intervention group and in control group could be reached and even maintained at follow-up. The Baden-Württemberg Study is one of the largest studies in Germany to investigate the efficacy of an overweight and obesity prevention program and to promote the physical, mental, and emotional abilities: baseline measurements were taken of 1947 pupils; about 80% of this number is expected to take part in the follow-up measurements. Thus, intervention effects can be investigated in subgroups, e.g. girls vs. boys, children with vs. children without migration background. Efficacy will be investigated with comparatively objective main outcomes. Power simulations showed that adequate power for an investigation of the three main outcomes will be maintained. Furthermore, the study cohort is large enough for an adjustment for possible covariates, e.g. variables regarding the familial and socio-economic background of children or time span between time of baseline measurement and time of follow-up measurement.

However, there are some limitations of the Baden-Württemberg Study. First of all, blinding is not feasible in such studies and therefore a bias in the assessment of main and further outcomes cannot be ruled out (especially with subjective outcomes). Furthermore, the control groups are subject to public awareness to the health topics and teachers are motivated which is part of the study commitment which contaminates study effects and decreases power. The program's intervention is a low threshold procedure. Thus, effects of intervention might only be measurable after a longer study period and the duration of the intervention (one academic year) could also be too short to show effects.

Moreover, children and parents with low socio-economic background or migration background might not be reached by the program due to language and social barriers. However, the program itself has an integrative and inclusive approach which focuses on the whole school class including all children with different abilities, all risk groups, different social background and minorities. Informative material for parents was translated into the languages of the two dominant groups of immigrants in Germany (Turkish and Russian). However, children and parents with low socio-economic background or migration background could not be represented adequately in the Baden-Württemberg Study itself because of lower rate of informed consent or lower understanding of the questionnaires. This effect cannot be quantified, although the proportion of migrants seems to be not different from the total population (data not shown). Furthermore, a lot of variables (especially in the parental questionnaire) are assessed subjectively and a check of plausibility is very limited. Objective measurement of physical activity using Actiheart^® ^and assessment of mental abilities using KiTAP are limited to two subsamples because of organizational, technical, and time reasons. The analysis of baseline data shows that in each subsample the distribution of sex, educational level, and intervention group is comparable with the whole population in the Baden-Württemberg Study (not shown).

The research team anticipates that not only efficacy regarding the main outcomes will be shown but positive effects concerning further health related outcomes will occur. It is also anticipated that this study contributes to answering questions regarding the possibilities and limits of school-based programs and about the conditions and consequences of health promotion in pupils. There are examples for initial effective short-term prevention programs that could not maintain their success at later follow-ups [55,56]. Over the course of the years effects attenuated or were restricted to subgroups. Thus, there is a need for prevention programs which run long term and can be applied comprehensively, in spite of schools' limited financial and personnel resources and may be applicable in a large scale at state or country level.

Therefore, a continuation of the Baden-Württemberg Study is planned as observational follow-up study: the pupils taking part in the study will be observed at least until they finish primary school. Measurements are planned in the periods from end of summer vacation until fall vacation in the respective academic years, i.e. at annual intervals. Long-term effects of the intervention of the program "Komm mit in das gesunde Boot - Grundschule" could be investigated this way.

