### Recruitment process and randomization process

Information about the program and Baden-Württemberg Study were issued during the academic year 2009/2010 using a number of ways, e.g. education and health authorities, and universities of education; electronic newsletter; television and radio; adverts in training catalogs for primary school teachers; participation at trade shows. The recruitment process was also promoted by ten informative events in different parts of Baden-Württemberg. Further, all primary schools of the state of Baden-Württemberg received written information about the program and the structure of the study, asking teachers to participate. Interested teachers contacted the program center. The participation in the program was voluntary, participating teachers had to agree with randomization. In total, written consent from 172 primary school teachers and principals at 94 schools was obtained (see Figure 2). Teachers who already took part in the program in the academic year 2009/2010 were not included in the study. Because the grade level (1^st ^grade vs. 2^nd ^grade) may play a key role for the efficacy assessment, stratification of randomization was carried out for grade level according to the following procedure. Based on information about the distribution of the 172 teachers within the 94 schools, stratification according to number of classes and grade level (grade) was realized for the randomization process: six different school types were identified and used as strata for randomization:

• Primary schools with only one class (only one 1^st ^grade)

• Primary schools with only one class (only one 2^nd ^grade)

• Primary schools with more than one class (only 1^st ^grades)

• Primary schools with more than one class (only 2^nd ^grades)

• Primary schools with more than one class (1^st ^grades and 2^nd ^grades)

• Primary schools with mixed-grade classes (i.e. classes with pupils from 1^st ^and 2^nd ^grade)

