### Power considerations

Power calculations were made at beginning of the study based on the availability of data for the main outcome parameters at baseline. Three main outcome parameters for the assessment of efficacy are specified in the study protocol: change in waist circumference, change in subscapular skinfold thickness and change in 6-min run performance, changes are calculated as differences between follow-up measurement and baseline measurement. All power calculations are based on simulations of hypothetic data and application of linear mixed effects models [51,52]. An adjustment according to Bonferroni was made to account for multiple testing [53]. In each mixed effects regression model only group (intervention group vs. control group) was used as explanatory variable and no distinction was made between several classes within the same school. Data from the project URMEL-ICE were used for specifying the differences between intervention group and control group. Randomization data were used for specifying the numbers of schools: IG: n = 44 schools, CG: n = 42 schools. Numbers of baseline measurements available for each primary outcome were used for calculation of pupil numbers in each study group:

• waist circumference: n = 1893 (IG: n = 1038, CG: n = 855)

• subscapular skinfold thickness: n = 1855 (IG: n = 1014, CG: n = 841)

• change in 6-min run performance: n = 1884 (IG: n = 1034, CG: n = 850)

Using this information, the following assumptions were made for the number of pupils in each school:

• change in waist circumference: IG: n = 24 (~1038 pupils in 44 schools); CG: n = 20 (about 855 pupils in 42 schools)

• change in subscapular skinfold thickness: IG: n = 23 (~1014 pupils in 44 schools); CG: n = 20 (about 841 pupils in 42 schools)

• change in 6-min run performance: IG: n = 24 (~1034 pupils in 44 schools); CG: n = 20 (about 850 pupils in 42 schools)

Furthermore, it was assumed that a percentage of 80% measurements available at baseline will be available at the follow-up, too. This percentage is an approximate value and was observed in the project URMEL-ICE.

The simulation results showed that the following values for statistical power could be reached if the assumptions proved right: 85% (change in waist circumference), 76% (change in subscapular skinfold thickness), and 74% (change in 6-min run performance).

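### The six randomisation strata are passed over in the article's covariate plans, while its one firm adjustment, sex, is justified by a baseline difference compatible with chance

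*Protocol article*

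**What the plan says.** **Design.** The section Recruitment process and randomization process explains that grade level "may play a key role for the efficacy assessment, stratification of randomization was carried out for grade level according to the following procedure". It then reports that "six different school types were identified and used as strata for randomization": one 1st-grade class only, one 2nd-grade class only, several 1st-grade classes, several 2nd-grade classes, several classes from both grades, and mixed-grade classes.

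**Power.** Under Power considerations, the simulated data were analysed with a reduced model: "In each mixed effects regression model only group (intervention group vs. control group) was used as explanatory variable". The number of clusters was "IG: n = 44 schools, CG: n = 42 schools".

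**Analysis.** Statistical considerations is open-ended: "For example, mixed effects regression models [52] or GEE models [54] will be used", and "Both procedures can be extended in an easy way to adjust for possible covariates". The examples given are family and social background and the time between the two measurements. The Discussion repeats essentially the same examples when it lists the study's strengths. Grade, number of classes and school type appear in neither place.

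**The one commitment.** The Discussion reports that boys are similarly represented in the two groups in 1st-grade and mixed-grade classes. It continues: "A difference in this percentage is observed within 2^nd ^grade classes (45.6% and 50.3"%). It concludes: "Therefore, an adjustment for sex will be realized in the statistical analysis".

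**The concern.** Two things look the wrong way round.

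First, the factors that restricted the randomisation are the natural first entries in the model, and the article itself says grade may matter. Stratifying removes between-stratum differences from the true sampling variance of the group comparison. A model without the strata still counts those differences as error. Its standard error is then too large for the design used, and the precision bought by stratifying is not collected.

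Second, the covariate that is committed to was chosen because its split looked uneven in one grade. Under randomisation, an observed imbalance is a poor guide to what belongs in the model. What matters is whether the variable predicts the outcome or was part of the design.

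At stake is precision. Two of the three stated powers (76% for subscapular skinfold, 74% for the 6-min run) are already below 80%.

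**Working it through.** **1. The sex imbalance.** Inputs are the group sizes and percentages of boys in Table 1 (Study sample at baseline). Rebuilding the counts of boys:

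- Intervention: 206 + 174 + 72 = 452, as stated in the text.
- Control: 181 + 154 + 53 = 388, as stated in the text.

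For 2nd grade, 174/382 = 45.5% (45.6% in the table) against 154/306 = 50.3%, a difference of 4.8 points. The pooled proportion is 328/688 = 0.477. The standard error is √[0.477 × 0.523 × (1/382 + 1/306)] = 0.0383, so z = 0.0478/0.0383 = 1.25 and p = 0.21. The same test gives p = 0.90 in 1st grade, p = 0.96 in mixed-grade classes and p = 0.39 overall (49.3% v 51.5%). Clustering is ignored throughout. These percentages describe the 1670 children with data at all three levels, not the 1855 to 1893 children with baseline values of the main outcomes.

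**2. The stated powers.** The figures of 85%, 76% and 74% cannot be reproduced, because the effect sizes, standard deviations and intraclass correlation (ICC) are not given. The article also does not say whether the simulated data contained any between-stratum variance.

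**3. What omission does to the standard error.** Let q be the share of the variance of the school-level comparison that the strata explain. Under stratified allocation the true variance is about (1 − q) times what a group-only model estimates, so the standard error is too large by a factor 1/√(1 − q). For assumed q of 0.05, 0.10 and 0.20 the factor is 1.03, 1.05 and 1.12. For q = 0 it is 1.

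**4. Illustrative simulation.** All of the following are assumptions except the total of 86 schools and the Bonferroni division by three:

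- 86 schools randomised within strata of 22, 18, 12, 10, 14 and 10 schools; 18 pupils per school.
- Two-sided level 0.05/3 = 0.0167; 4000 runs per setting.
- Regression of school means with and without strata.
- Share s of total variance due to strata; within-stratum ICC ρ. Then q = s / [ρ + s + (1 − ρ − s)/18]. For ρ = 0.02 and s = 0.01 this is 0.01/0.0839 = 0.12.

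| ρ | s | q | Type I error, without / with strata | Power, without / with strata |
|---|---|---|---|---|
| 0.02 | 0 | 0 | 0.016 / 0.016 | 73% / 73% |
| 0.02 | 0.01 | 0.12 | 0.013 / 0.018 | 75% / 80% |
| 0.02 | 0.03 | 0.29 | 0.005 / 0.018 | 78% / 89% |
| 0.02 | 0.05 | 0.41 | 0.001 / 0.018 | 80% / 95% |
| 0.05 | 0 | 0 | 0.017 / 0.017 | 75% / 76% |
| 0.05 | 0.01 | 0.09 | 0.013 / 0.020 | 76% / 79% |
| 0.05 | 0.03 | 0.23 | 0.006 / 0.015 | 75% / 85% |
| 0.05 | 0.05 | 0.33 | 0.004 / 0.018 | 77% / 90% |

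The effect size was reset in each row, so compare within rows only. Without strata the test becomes conservative as s grows; with strata it stays near nominal. At s = 0 nothing is gained or lost beyond simulation error. The table shows direction and mechanism; it does not estimate this trial's power.

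**The case against.** The strongest reply is that nothing has been fixed wrongly. The group-only model was fitted to hypothetical data to obtain power. The analysis is described separately, by examples, and already goes beyond group because sex will be added. A full protocol or analysis plan that is not shown may well include the strata. This stands: a reader might infer that the primary analysis omits the strata, but no sentence says so. What remains is what the article does state, namely a covariate commitment made on observed imbalance, beside example lists that skip the design factors.

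Sex stays in the model either way, and the choice was published before analysis began: Actual status of study says follow-up was complete and data checks were still to come. That also stands. No bias from adjusting for sex is shown, and the sentence is not limited to one grade or outcome. Only the reason given is at fault.

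The main outcomes are changes from baseline, so constant differences in level between grades cancel. Only differences in one-year change matter, and the article gives no figure for them. This is correct, and it is why the loss could be zero.

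A reader might also apply the factors in step 3 to the stated powers and claim, for instance, that the 6-min run would rise above 74%. The documents do not support this. It presumes that the simulated data carried stratum variance. The only empirical source named is the precursor study, which enrolled 2nd grade only and so holds no between-grade variance. If the simulated data had none, modelling the strata would protect the stated powers, not raise them.

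**Conclusion.** The point holds in a limited form. The strata are passed over, not proven excluded, and the single committed covariate rests on a difference compatible with chance (p = 0.21, ignoring clustering). If school type predicts one-year change in waist circumference, skinfold or running performance, a model without it gives standard errors that are too wide and a conservative test.

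A reader might suspect inflated type I error; the opposite holds, and the harm is confined to lost power. Its size is unknown. It depends on variance shares, an ICC and stratum sizes that the article does not report, and it is nil if the strata explain none of the change. No specific gain over the stated 74% to 85% should be claimed. This is a nearly free improvement, not a flaw that threatens the validity of the result.

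**What to change.** State that every primary model includes school-type stratum as fixed effects: all six categories or, at minimum, grade (1 / 2 / mixed) and single-class v multi-class school. State that sex is a prespecified prognostic covariate for all grades and all three main outcomes, and drop the observed 2nd-grade difference as the reason.

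Six strata add five parameters. In a school-level comparison of 86 schools, residual degrees of freedom fall from 84 to 79; with the 84 schools at follow-up, from 82 to 77. The stratum of each school is in the randomisation list, so no new data are needed, and the article reports that analysis had not yet started.
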